### Intervention description {11a}

The SGT group’s regimens will be selected according to *H. pylori* susceptibility to clarithromycin and levofloxacin. Participants will undergo an upper endoscopy to provide gastric mucosal samples for molecular testing. The test is based on polymerase chain reaction (PCR), which detects *H. pylori* mutations associated with clarithromycin and levofloxacin resistance. The susceptibility testing PCR protocol is outlined in Additional File 1. Regimens for the first-line treatments are based on clarithromycin susceptibility: If the *H. pylori* strain is sensitive to clarithromycin, we will administer clarithromycin triple therapy—esomeprazole (20 mg, twice daily), clarithromycin (500 mg, twice daily), and amoxicillin (1.0 g, twice daily)—for 14 days, as per the recommended guideline [17]. If the strain is clarithromycin resistant, we will administer the HDDT regimen because a network meta-analysis revealed that this treatment is the most optimal first-line therapy for *H. pylori* among the Asian population [24]. If the first-line treatment fails, rescue therapy will be selected according to levofloxacin susceptibility. If the *H. pylori* strain is levofloxacin sensitive, we will administer the levofloxacin quadruple regimen—esomeprazole (20 mg, twice daily), levofloxacin (500 mg, once daily), amoxicillin (1.0 g, twice daily), and colloidal bismuth pectin (150 mg, four times daily)—for 14 days, as per the recommended guideline [17]. If *H. pylori* is levofloxacin-resistant, we will administer the furazolidone quadruple regimen—esomeprazole (20 mg, twice daily), furazolidone (100 mg, twice daily), amoxicillin (1.0 g, twice daily), and colloidal bismuth pectin (150 mg, four times daily)—for 14 days. This furazolidone regimen can provide a satisfactory eradication rate in patients with multiple treatment failures and does not increase the incidence of adverse events [25, 26].

### Criteria for discontinuing or modifying allocated interventions {11b}

The safety of *H. pylori* eradication treatments is well defined, where taste disturbance, diarrhoea, nausea, and abdominal pain are the most frequent adverse events (AEs). The majority of AEs are mild and temporary. It is estimated that only 1.3% of patients discontinue treatment due to AEs [27]. In our study, when participants report AEs, they will be evaluated by the investigators. The study drugs may be discontinued for any of the following reasons: participants experience severe AEs, are declared unsuitable for continued drug use, or cannot comply with the study procedures. Participants may withdraw from the study for any reason at any time. The reasons for withdrawal will be recorded if disclosed by the participants.

### Strategies to improve adherence to interventions {11c}

Face-to-face adherence reminder sessions will take place during the initial drug dispensing. Sessions will cover the importance of participants completing treatment regimens and calling investigators if experiencing problems that may be related to study drugs. Moreover, participants will receive instructions on taking study pills (dose, timing, storage) and what to do in the event of a missed dose. Furthermore, participants will receive a compliance reminder phone call 1 week after the start of treatment, and a 13C-UBT test reminder call 4 weeks after the end of treatment.

### Relevant concomitant care permitted or prohibited during the trial {11d}

During the study procedure, the use of all other antibiotics, proton-pump inhibitors (PPIs), H2 receptor antagonists, nonsteroidal anti-inflammatory drugs, Chinese traditional herbs, and probiotics will be prohibited.

### Provisions for post-trial care {30}

No specific post-trial care is planned, as the study is a low-risk intervention. The study site has insurance to cover for harms associated with the trial. This includes cover for additional health care, compensation, or damages.

### Outcomes {12}

The primary outcome of the study is the proportion of participants with successful *H. pylori* eradication. This will be determined according to the results of 13C-UBTs performed at least 4 weeks after the end of the first-line treatment period between the SGT and ET groups.

The secondary outcomes: The rescue treatment and the overall eradication rates in the SGT and ET groups. The eradication rate of HDDT for the clarithromycin resistance group and the empirical BQT failure group. Frequency of AEs and the rate of compliance between the SGT and ET groups.

### Participant timeline {13}

The schedule of enrolment, interventions, and assessments are summarised in Fig. 2.

**Fig. 2 Fig2:**
[figure not shown]
Study schedule of enrolment, intervention, and assessments. AEs: Adverse events; SGT: Susceptibility-guided therapy; UBT: Urea breath test

### Sample size {14}

We will conduct this as an equivalence study, and the calculation of the sample size is based on the primary outcome, which is the first-line eradication rate of *H. pylori*. Using intention-to-treat (ITT) analysis, a meta-analysis comparing SGT vs. BQT as the first-line treatment for *H. pylori* infection found that the pooled eradication rates of SGT and BQT were 86% vs. 78% [12]. A recent meta-analysis reported that the overall eradication rate in patients harbouring susceptible strains was 95.0% (95% CI [94.1–95.9]), but only 63.4% of treatment arms (64/101) achieved good eradication rates (≥ 90%) [14]. Based on these data, our assumption is a 90% eradication rate of susceptibility‐guided sequential strategy, 80% eradication rate of empiric therapy, power of 80%, alpha of 0.05 (two-sided), and allocation ratio of 1:1. The calculated sample size is 197 participants per arm. Considering a dropout rate of 20%, we have to recruit at least 494 patients (247 participants per arm) for the study. Therefore, we aim to recruit 500 participants for this study.

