In our study design, AST guides both the first-line and rescue therapies. A sequential strategy should focus not only on the first-line treatment, but also on a consecutive rescue treatment regimen after first-line failure. At the same time, the choice of treatment regimens should be based on local susceptibility, updated guidelines, and recent RCT results [17–20]. Clarithromycin resistance is the main factor to consider when deciding which regimen to use for *H. pylori* infections; thus, for the first-line treatment, we chose therapy regimens based on clarithromycin susceptibility. After first-line treatment failure, fluoroquinolone-containing quadruple (or triple) therapy may be recommended, as per the Maastricht VI/Florence consensus report [17]. Therefore, for the rescue treatment, we chose therapy regimens based on levofloxacin susceptibility. We hypothesise that, compared with empirical therapy, the susceptibility-guided sequential strategy will demonstrate a higher eradication rate for *H. pylori* infection.

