## Objectives {7}

The main objective of this trial is to assess whether a sequential strategy based on molecular AST for *H. pylori* infection will have a better eradication rate than an empirical therapy (ET).

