## Trial design {8}

This trial is designed as a prospective, single-centre, randomised, open-label, active-controlled equivalence study with a 1:1 allocation ratio. The study procedure is detailed in Fig. 1.

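### The protocol calls the trial an equivalence study, but its aim, sample size and analysis are those of a superiority trial and it gives no margin; the label should be corrected

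*Protocol article*

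**What the plan says.** Two sections of the protocol article that define the design name it as equivalence. Trial design {8} describes an "active-controlled equivalence study with a 1:1 allocation ratio". Sample size {14} opens with "We will conduct this as an equivalence study, and the calculation of the sample size is based on the primary outcome".

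The aim points the other way. Background and rationale {6a} hypothesises that "the susceptibility-guided sequential strategy will demonstrate a higher eradication rate". Objectives {7}, like the abstract, asks whether the guided strategy has the better rate.

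The inputs in Sample size {14} are: "our assumption is a 90% eradication rate of susceptibility‐guided sequential strategy, 80% eradication rate of empiric therapy", with 80% power, two-sided alpha of 0.05 and 1:1 allocation. The results are 197 per arm, 247 per arm after 20% dropout, and a recruitment target of 500. No margin is among the inputs.

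Statistical methods {20a} plans a point estimate and two-sided 95% confidence interval (CI) for the SGT minus ET difference by the Miettinen-Nurminen method, with significance at P < 0.05. It names ITT, modified ITT (mITT) and per-protocol (PP) sets. A missing breath test counts as failure. No equivalence bounds appear there or in Methods for additional analyses {20b}.

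**The concern.** Equivalence and superiority have opposite null hypotheses. A superiority trial starts from no difference and tries to reject it. An equivalence trial starts from a difference at least as large as a margin and tries to rule that out. A trial sized on a true 10-point difference is built to find a difference, so calling it an equivalence study contradicts its own planning assumption.

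What is at stake is how a null result will be read. The background section cites one meta-analysis in which SGT and bismuth quadruple therapy had similar first-line efficacy in high-resistance areas, and another in which SGT did not appear better than empirical first-line quadruple therapy. A non-significant result is therefore plausible. Under an equivalence label with no margin, nothing in the plan stops it from being reported as equivalence shown.

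The label also affects which analysis set carries the claim. ITT is the usual primary set for superiority, while PP has more weight in equivalence. The two sets can diverge here, because PP drops participants without a repeat breath test whom ITT counts as failures.

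**Working it through.** **1. Reproducing the plan's figure.** Inputs from Sample size {14}: 90% and 80%, two-sided alpha 0.05 (z = 1.960), power 80% (z = 0.8416), 1:1.

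- Superiority, unpooled variance: n = (1.960 + 0.8416)² × (0.9 × 0.1 + 0.8 × 0.2) / 0.10² = 7.849 × 0.25 / 0.01 = 196.2, rounded up to **197 per arm**. This matches exactly.
- Dropout: 197 / (1 − 0.20) = 246.25, rounded up to **247 per arm**, or 494 in total. This also matches exactly.
- The pooled-variance version gives 199, so the match does not depend much on the choice of formula.

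No margin is needed to obtain these figures.

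**2. What an equivalence calculation would need.** With truly equal rates p, margin m, 80% power and a 95% CI required to lie within ±m, n = 2p(1 − p)(1.960 + 1.2816)² / m². The protocol gives no m, so the margins below are assumptions.

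| Assumed margin | p = 80% | p = 85% | p = 90% |
|---|---|---|---|
| 5 points | 1345 | 1072 | 757 |
| 10 points | 337 | 268 | 190 |
| 15 points | 150 | 120 | 85 |

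The range of 85 to 1345 per arm shows that an equivalence size cannot be recovered from the document.

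**3. What a non-significant result would mean.** At the planning rates with 250 per arm, the standard error is √(0.25/250) = 0.0316, so the 95% CI half-width is 1.96 × 0.0316 = 6.2 points. Suppose, as an illustration, that the observed difference is 5 points. The interval is then about −1.2 to 11.2 points. That is not significant, yet it does not exclude the 10-point advantage on which the trial was planned. Calling it equivalence would be wrong under any margin of 10 points or less.

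**4. Power as a superiority trial, 250 per arm.**

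- If 90% and 80% are ITT rates that already count missing tests as failures: about 88% (88.2% pooled, 88.5% unpooled).
- If they are rates among those tested, and 20% are missing in each arm (assumption): ITT rates become 0.9 × 0.8 = 72% and 0.8 × 0.8 = 64%, and power is about 48% (48.3%, pooled).

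**The case against.** The strongest reply is that only one word is wrong. The hypothesis, objective, sample size inputs and planned analysis (95% CI of the difference, P < 0.05) all fit superiority. The abstract's design sentence omits equivalence, and no equivalence test of the primary outcome is planned. This stands. A reader might infer that the trial cannot reach the conclusion it seeks, or that nobody could tell what counts as success. The documents do not support that: only the label fails, and the operative plan can test superiority.

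A reader might also quantify the damage by noting that, with a true 10-point difference, the 95% CI would fall within an assumed ±10-point margin only 2.5% of the time. That figure holds by construction, since the true difference sits on the boundary, and it describes a test that nobody plans. It does not measure harm to this trial.

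Finally, the ranking of ITT, mITT and PP is commonly left to a full protocol or analysis plan. It is not counted here as a separate defect. It matters only because the label bears on it.

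The reply does not remove the contradiction. The label appears in both sections that define the design, and a margin is a required input to any equivalence sample size. An analysis plan that is not shown cannot reconcile these statements.

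**Conclusion.** The concern holds as a wrong design label with a real reporting risk. Trial design {8} and Sample size {14} should not say equivalence, given a superiority objective and hypothesis, a superiority sample size reproduced exactly at 197 and 247 per arm, and no margin.

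It would be too much to infer that relabelling leaves the trial with about 88% power in every case. That figure rests on 90% and 80% being ITT rates net of missing tests. The 86% and 78% cited in Sample size {14} are ITT rates, which supports that reading. The 20% dropout inflation suggests the other, under which power falls to about 48% if 20% are missing in each arm. The document does not settle which applies.

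Superiority is the better-supported intention, but equivalence is written twice, so the sponsor should confirm it. Nothing can be said about the wording of the registry record, which is not at hand.

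**What to change.** Before the data are analysed:

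- Replace equivalence with superiority in Trial design {8} and Sample size {14}.
- State the null hypothesis: first-line eradication difference (SGT minus ET) = 0, two-sided alpha 0.05.
- Define success as a lower limit above 0 for the Miettinen-Nurminen 95% CI in the ITT set, with mITT and PP supportive.
- State that a non-significant result will not be reported as equivalence.
- Confirm whether the assumed 90% and 80% already count missing breath tests as failures. If they do, 197 and 247 per arm stand as a superiority size. If they do not, the sample size justification has to be revisited.

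If the sponsor really intends equivalence, the protocol instead needs a justified margin, a rule that the CI must lie within the bounds, and a new sample size calculation.

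Cost: for superiority with rates confirmed as ITT rates, a wording amendment only, with no change to recruitment or conduct.

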## Statistical methods

### Statistical methods for primary and secondary outcomes {20a}

The eradication rate of *H. pylori* will be evaluated using ITT, mITT (including all participants who received at least one dose of the study drug), and per-protocol (PP) analyses (including participants who had good compliance and were re-examined by 13C-UBT). A point estimate and two-sided 95% CI of the difference in eradication rates between the SGT and ET groups will be calculated via the Miettinen & Nurminen method for the primary and secondary outcomes. Participants who have not undergone a re-examined 13C-UBT will be considered as treatment failures, i.e., ‘not eradicated,’ in the statistical analysis. Propensity score analysis will be used to adjust for differences in treatment regimens and potential confounding factors. Compliance and sensitivity analyses will be conducted to compare the treatment responses between compliant and non-compliant participants and determine if there is a significant association between compliance and treatment outcomes. Statistical significance will be set at *P* < 0.05.

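### The 20% dropout inflation assumes that dropouts leave the analysis, but the plan counts untested participants as failures, so the stated 80% power does not carry over to ITT

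*Protocol article*

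**What the plan says.** Sample size {14} of the protocol article gives all the planning inputs. For the susceptibility-guided arm (SGT), "our assumption is a 90% eradication rate of" the sequential strategy; for the comparator, "80% eradication rate of empiric therapy". The remaining settings are "power of 80%, alpha of 0.05 (two-sided), and allocation ratio of 1:1". These yield 197 per arm. The section then allows for loss: "Considering a dropout rate of 20%, we have to recruit at least 494 patients (247 participants per arm) for the study". The target is rounded to 500, or 250 per arm.

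Two sources are cited for the rates. One is a meta-analysis described as an ITT comparison, which "found that the pooled eradication rates of SGT and BQT were 86% vs. 78" per cent. The other gives 95.0% for patients with susceptible strains. The section does not say whether the adopted 90% and 80% are ITT rates or rates among participants with a test result. It does not define dropout.

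Statistical methods {20a} names three analysis sets: ITT, modified ITT (at least one dose) and per-protocol (good compliance and a repeat test). On missing results it says: "Participants who have not undergone a re-examined 13C-UBT will be considered as treatment failures". The section on non-adherence and missing data {20c} repeats the rule. Neither section says which set is primary.

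**The concern.** Dividing by one minus the dropout rate is the right adjustment when dropouts leave the denominator, because it restores the number of participants with a result. It does not suit a rule that keeps dropouts in the denominator as failures. There the number analysed never falls. Instead, both eradication rates shrink, and so does the difference between them. Recruiting 247 rather than 197 per arm offsets only part of that loss.

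Readers will rely on the 80% power statement when they interpret the ITT result. If that power is much lower under the plan's own dropout figure, a non-significant ITT difference is weak evidence against susceptibility testing, yet the document would present it as coming from an adequately powered comparison.

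**Working it through.** **Inputs.** From Sample size {14}: rates 90% and 80%, two-sided alpha 0.05, power 80%, ratio 1:1, dropout 20%, target 500. From Statistical methods {20a}: a missing repeat test counts as failure.

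**Step 1: reproduce the plan's figures.** Unpooled two-proportion formula:

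n = [0.90×0.10 + 0.80×0.20] × (1.960 + 0.842)² / 0.10² = 196.2, so 197 per arm. This matches. (The pooled-variance version gives 199.)

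Inflation: 197 / 0.80 = 246.25, so 247 per arm and 494 in total. This matches. There is no arithmetic slip.

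**Step 2: what the inflation preserves.** With 250 per arm and 20% untested, 250 × 0.80 = 200 per arm have a result. At 90% vs 80%, power among 197 to 200 tested per arm is about 80%, as stated. That holds for an analysis that removes the untested.

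**Step 3: ITT, if 90% and 80% are rates among tested participants.** With an untested share d, equal in both arms and counted as failures, each rate is multiplied by (1 − d). At d = 0.20:

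- SGT: 0.90 × 0.80 = 0.72
- Empirical therapy: 0.80 × 0.80 = 0.64
- Difference: 8 points instead of 10

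Normal approximation at 250 per arm: SE = √[(0.72×0.28 + 0.64×0.36)/250] = √(0.432/250) = 0.0416. Then 0.08/0.0416 = 1.92, and Φ(1.92 − 1.96) is about 0.49. Exact binomial enumeration of the score test that underlies the planned Miettinen–Nurminen interval gives 48.4% (47.9% at 247 per arm).

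The same exact calculation at 250 per arm for other untested shares:

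| Untested in each arm | ITT rates | Difference (points) | ITT power |
|---|---|---|---|
| 0% | 90.0% vs 80.0% | 10.0 | 88.7% |
| 5% | 85.5% vs 76.0% | 9.5 | 77.3% |
| 10% | 81.0% vs 72.0% | 9.0 | 66.4% |
| 15% | 76.5% vs 68.0% | 8.5 | 56.7% |
| 20% | 72.0% vs 64.0% | 8.0 | 48.4% |

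Power is 80.8% at 3.5% untested and 79.6% at 4.0%, so 80% needs less than about 4% untested.

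**Step 4: ITT, if 90% and 80% are already ITT rates.** Missing tests are then already inside the rates and no inflation is needed. Power at 250 per arm is 88.2% (pooled approximation), 88.5% (unpooled) or 88.7% (exact). But if 20% of an arm counts as failure for want of a test, its ITT rate cannot exceed 1 − 0.20 = 80%, so 90% is out of reach. If eradication among tested participants is the cited 95%, a 90% ITT rate requires (1 − d) × 0.95 = 0.90, so d = 1 − 0.90/0.95 = 5.3%.

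**The case against.** The strongest reply is that 48% is conditional. It needs three things together: 90% and 80% are rates among the tested; the full 20% lacks a breath test, equally in both arms; and ITT is the deciding analysis. The document fixes none of these.

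- One cited source is an ITT comparison, which points towards ITT rates and a power of about 88–89%.
- Dropout is undefined. The per-protocol set also excludes participants with fewer than 10 days of treatment. If the 20% was meant to cover them too, those who are tested stay in ITT with an observed result, and the untested share is smaller. The plan also provides reminder calls and appointment scheduling for the breath test.
- In a per-protocol analysis the untested do leave, and dividing by 0.8 is then the correct step.

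All of this stands as a limit on the size of the effect. A reader might infer that the trial simply has 48% power, or that the 90% rate is impossible outright. The documents support neither without those conditions. The reply does not rescue the section as written, though. Applying the inflation to the stated rates implies that they are rates among the tested, and ITT then falls short at the planned 20%. Reading them as ITT rates makes the inflation unnecessary and puts 90% in conflict with 20% counted as failures.

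**Conclusion.** The point holds in conditional form. The arithmetic is correct, but the dropout adjustment does not match the missing-equals-failure rule, so the stated 80% power cannot be carried over to the ITT analysis at the planned dropout.

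If 90% and 80% are rates among tested participants and 20% of each arm has no repeat test, ITT power at 250 per arm is about 48%. If they are ITT rates, it is about 88–89%, with an untested share that must be far below 20%. For an analysis restricted to about 200 tested per arm, 80% is right. The document does not let a reader choose between these. Because it gives the rates, the inflation and the missing-data rule itself, the inconsistency does not depend on any document that is not shown.

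**What to change.** Keep 500 participants and rewrite Sample size {14}. State which analysis set the power refers to, whether 90% and 80% are rates among tested participants or ITT rates, and that the 20% means participants with no repeat 13C-UBT. Then take one of two routes:

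- **(a) Rates among tested participants.** State that 80% power applies to about 200 tested per arm, and report ITT power at 250 per arm by untested share: 89%, 77%, 66%, 57% and 48% at 0%, 5%, 10%, 15% and 20%.
- **(b) ITT rates.** Delete the inflation, state power of about 88–89% at 250 per arm, and give an untested share compatible with a 90% ITT rate: at most about 5% if eradication among tested participants is 95%. Asking only for less than 10% would be too loose: at 9% untested, eradication among the tested would have to be 0.90/0.91 = 98.9%.

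The cost is text only; recruitment, data collection and the missing-data rule stay as they are. The downside is that the stated ITT power may look less favourable.
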